### 4.2. Trial Protocol Registration

The study protocol adheres to the Standard Protocol Items: Recommendations for Interventional Trials (SPIRIT) guidelines. Ethical approval was granted by the Regional Committee for Medical Research Ethics at the Medical University of Lodz. The study is registered with ClinicalTrials.gov (NCT06917300; 7 April 2025), under the unique protocol ID RNN/02/24/KE, and with the Clinical Trial Department of the Medical University of Lodz.

### 4.3. Participant Sample and Sample Size

#### 4.3.1. Recruitment and Allocation

The sample size calculation is based on detecting a clinically meaningful reduction in preoperative anxiety measured by the State-Trait Anxiety Inventory–State (STAI-S) score, which is the primary endpoint. The trial was powered based on the primary endpoint of STAI-S change. Prior VR perioperative studies report a mean reduction of 8–10 points with a standard deviation of approximately 10 points. Using Rosner’s formula for three parallel study arms, with α = 0.05, power = 0.80, and a minimum clinically significant difference of 8 points, 42 patients per arm are required. To account for an anticipated 15% attrition rate, we will enroll 50 participants per arm, for a total sample size of 150 patients. Elective procedures are defined as those happening the day after the initial patient evaluation. All patients will be provided with written informed consent, and the trial procedures will be explained verbally and in writing to all patients prior to study enrolment.

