### 4.9. Statistical Analysis

The statistical analysis will be performed under the mentorship of a biostatistician experienced in neurosurgical research. The nominal data will be presented as *n* (% of the total). The dependencies between them will be assessed using the test chosen based on the size of the smallest sample. All analyses will follow an intention-to-treat approach. The primary endpoint (change in STAI-S score from baseline to immediately postintervention) will be analyzed using one-way ANCOVA adjusted for baseline STAI-S. Pairwise comparisons will be Bonferroni-corrected. Secondary outcomes will be analyzed as follows: VAS pain at 24 h (ANCOVA adjusted for opioid dose), total opioid consumption (ANOVA or Kruskal–Wallis depending on distribution), patient satisfaction (Kruskal–Wallis), and rescue analgesic use (χ^2^ test). Longitudinal measures (baseline → post-VR → postoperative) will be evaluated with a linear mixed-effects model including group, time, and group × time interaction. Normality will be tested using the Shapiro–Wilk test. Missing data will be assessed for pattern and mechanism. Multiple imputation (m = 10) will be used if appropriate. Longitudinal analyses will primarily rely on linear mixed-effects models, which are robust to missing observations under missing-at-random assumptions. The primary comparison will evaluate procedural/educational VR versus standard care with respect to STAI-S score change. Secondary comparisons will include relaxation/distraction VR versus standard care and procedural/educational VR versus relaxation/distraction VR. Postoperative pain analyses will additionally be adjusted for perioperative opioid consumption and surgery duration when appropriate. Statistical analysis will be performed using STATISTICA 13.1 (TIBCO, Palo Alto, Santa Clara, CA, USA) and two-sided α = 0.05.

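### The 42 patients per arm cannot be reproduced from the stated inputs, which give 25–26 per arm (33–35 with Bonferroni for three comparisons)

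*Protocol article*

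**What the plan says.** Section 4.3.1 of the protocol article sizes the trial on the primary endpoint: "The trial was powered based on the primary endpoint of STAI-S change". The variability comes from earlier work: "Prior VR perioperative studies report a mean reduction of 8–10 points with a standard deviation of approximately 10 points". The design settings are given as "for three parallel study arms, with α = 0.05, power = 0.80", with Rosner's formula named as the method, and the result is "a minimum clinically significant difference of 8 points, 42 patients per arm are required". A 15% attrition allowance then leads to "we will enroll 50 participants per arm, for a total sample size of 150 patients".

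Section 4.9 adds three facts that bear on the calculation. The test level is "two-sided α = 0.05". The primary comparison is a single pairwise contrast, educational VR against standard care. Pairwise comparisons are to be Bonferroni-corrected. Section 4.3.1 itself mentions no adjusted α.

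**The concern.** The paragraph prints every input the usual formula needs, and also prints the result, but the two do not agree. A standardised difference of 8/10 = 0.8 is large and needs about 25 patients per arm at 80% power. The printed 42 is roughly 60% higher.

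This is the only sample size justification shown, and it concerns the primary endpoint. The power statement tells a reader what a non-significant primary result would mean. As written, either the trial has clearly more power than stated for 8 points, or it was sized on an SD, α or power that is not printed. These possibilities lead to different readings of a null result.

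There is also a smaller point of wording. The 8–10 points are described as a mean reduction, whereas the formula needs a difference between arms. The text never says outright that the 8 points are such a difference.

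**Working it through.** **Inputs.** From 4.3.1: difference 8, SD about 10, α 0.05, power 0.80, three arms of equal size, attrition 15%. From 4.9: two-sided testing, one primary pairwise contrast, Bonferroni for pairwise comparisons.

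**Step 1: attempt to reproduce 42.** The formula per arm is n = 2 × ((z for α + z for power) × SD / difference)².

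- α 0.05 two-sided: 2 × ((1.960 + 0.842) × 10/8)² = 24.5, so 25. The t-test gives 25.5, so 26.
- α 0.05/3 = 0.0167: 2 × ((2.394 + 0.842) × 10/8)² = 32.7, so 33. The t-test gives 34.2, so 35.

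**Step 2: other ordinary readings at 80% power.**

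| Reading | Patients per arm |
|---|---|
| One-sided α 0.05 | 20–21 |
| Bonferroni for two comparisons (α 0.025) | 30–31 |
| Three-group F test, means 0, 0, 8 | 24 |
| Three-group F test, means 0, 4, 8 | 32 |

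None reaches 42.

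**Step 3: the attrition step.** 42 / (1 − 0.15) = 49.4, so 50. This step is correct, so the discrepancy lies in the 42 itself.

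**Step 4: what would give about 42.** Each line changes at least one printed input.

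| Changed input | Result |
|---|---|
| Power 0.95, α 0.05 | 40.6 (t-test 41.6) |
| Power 0.90, α 0.0167 | 42.2 (t-test 43.7) |
| SD needed at power 0.80, α 0.05 | 13.1 (t-test 12.9) |
| SD needed at power 0.80, α 0.0167 | 11.3 (t-test 11.1) |

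**Step 5: what 42 evaluable per arm delivers with SD 10** (t-test).

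| α for the primary comparison | Power for 8 points | Difference detectable with 80% power |
|---|---|---|
| 0.05 | 95% | 6.2 points |
| 0.0167 | 89% | 7.2 points |

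**The case against.** The best defence is that the paragraph may be incomplete rather than mistaken. The SD is only approximate, and 4.9 prescribes Bonferroni. At α 0.0167 and 80% power, an SD of 11 gives 41.0 per arm by t-test, close to 42. Another route takes SD 10 as the spread at a single visit. With a pre–post correlation of 0.15, the change-score SD is 10 × √(2 × 0.85) = 13.0, and the normal formula gives 24.5 × 1.7 = 41.7. The article states neither route. Section 4.3.1 prints α 0.05 without adjustment and ties the SD to the reported reduction. This defence therefore does not rescue the text. It does limit the conclusion to saying that the figure is not reproducible as stated, because it cannot be shown which input is at fault.

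A second defence is that the discrepancy favours the trial. That stands if SD 10 is right, but the unexplained 42 is itself a reason to ask whether SD 10 was the planning value.

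The defence on wording also has weight: a minimum difference quoted in a calculation for parallel arms reads naturally as between-arm. That part is a clarification only.

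**Conclusion.** The 42 per arm does not follow from the inputs printed beside it. They give 25–26 per arm, or 33–35 with Bonferroni for three comparisons. If the difference of 8 and SD of 10 hold, the true power at 42 evaluable per arm is about 95% (α 0.05) or 89% (α 0.0167), and the stated 80% is too low. If the planners used an SD near 13, or near 11 with Bonferroni, the published SD is wrong and 80% is the right power. These figures assume two equal arms compared by a t-test, with no gain credited for the baseline adjustment in the planned ANCOVA.

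Two stronger readings should be resisted. A reader might infer that the trial is underpowered for its primary comparison; on the stated inputs the opposite is true. A reader might also take the 8–10 points as the expected effect of each VR arm, conclude that the two VR arms differ by at most 2 points, and call that contrast hopeless. The article attributes the 8–10 points to earlier VR studies, assigns the range to neither arm, claims no power for the VR-versus-VR contrast and makes no equivalence claim.

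**What to change.** Keep 50 per arm and correct the justification in 4.3.1 in one of two ways.

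1. If 42 came from other inputs, print the α (with any Bonferroni factor), the SD and the power actually used.
2. If not, restate what 42 evaluable per arm provide with SD 10 and a difference of 8, at the α that applies to the primary comparison. If it is tested at two-sided 0.05, that is 95% power, with 80% power for 6.2 points. If it is Bonferroni-corrected for three comparisons, it is 89% power, with 80% power for 7.2 points. Section 4.9 should make clear which α applies, so that the two sections agree.

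In either case, add that the 8 points are the between-arm difference in STAI-S change.

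The cost is one reworded paragraph, plus a clarifying phrase in 4.9 if needed. Enrolment and the planned analysis do not change.

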#### 4.3.2. Study Group Selection

The following inclusion and exclusion criteria (Table 1) were systematically established in order to guide the recruitment process and determine eligibility for enrolment in this trial.

### 4.4. Randomization

Eligible patients will be randomly assigned to the VR group, the control group (standard preoperative care), and the VR relaxation/distraction group. Randomization will be performed using a computer-generated permuted block randomization sequence (block size = 6) created by a statistician not involved in patient recruitment or assessment. Allocation concealment will be ensured using sequentially numbered, opaque, sealed envelopes opened only after enrolment. Participants cannot be fully blinded to VR exposure; however, they will be informed that two different VR experiences are under investigation without emphasis on superiority. Outcome assessors and data analysts will remain blinded to treatment allocation. An active comparator VR relaxation/distraction group is included to minimize expectancy and attention-related bias.

After obtaining the patients’ consent and agreement to undergo surgery, the randomization and allocation sequence will be carried out blindly by an independent research assistant during the clinic visit. The researcher conducting interviews and collecting the primary and secondary outcome data will be blind to the group assignments.

To minimize selection bias, randomization will be performed by an investigator independent of patient recruitment and assessment, and outcome assessors and data analysts will remain blinded to group allocation. Participants will be informed that both interventions are active and under evaluation without emphasis on superiority. To reduce the risk of dropout, all participants will receive equal attention and standardized information regarding the importance of study participation. The VR intervention will be administered on the day prior to surgery in a quiet preoperative preparation room.

To prevent any setbacks, a limited number of people will be included to interact with the patients, and a reminder will be given to the patients not to discuss the trial procedure and allocations. In addition, the experiment room will be different from the regular patients’ rooms. In the experiment room, the patients will be exposed to VR content, with respective psychological and physiological assessments. After that, the patients will be instructed to go back to their hospital rooms.

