## 3. Objectives

The aim of this research study is to evaluate the impact of immersive VR exposure on preoperative anxiety and pain, and, additionally, to assess whether VR intervention would significantly alleviate pain and anxiety levels of patients undergoing complex spinal surgeries. We hypothesize that the application of preoperative VR-based intervention will alleviate anxiety and pain both pre- and postoperatively when it is used as treatment to complement standard care compared to standard routine care alone, and that it may lead to better outcomes and higher satisfaction in patients. The primary objective is to evaluate whether procedural/educational VR reduces preoperative anxiety compared with standard care. Secondary objectives include comparing relaxation/distraction VR versus standard care, and procedural/educational VR versus relaxation/distraction VR with respect to postoperative pain, analgesic use, and patient satisfaction.

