## 4. Material and Methods

### 4.1. Trial (Study) Design

This is a single-center study prospective, randomized, placebo-controlled trial with three parallel groups of adult patients (18 to 70 years) who have degenerative spinal disorders, specifically those diagnosed with lumbar or cervical spondylosis who are scheduled to undergo spinal fusion, discectomy, decompression, or stabilization procedures. Relevant surgical variables, including cervical/lumbar/thoracic location, type of surgery, surgical approach, duration of surgery, and perioperative complications, will be prospectively recorded and considered in adjusted analyses. The study assesses the influence of a single preoperative VR (exposure) session and its effect on both preoperative and postoperative anxiety and pain, as well as reported functional outcomes in patients undergoing elective spine surgery.

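### The trial is labelled placebo-controlled but has no placebo arm, and the arm included against expectancy bias lies outside the primary anxiety comparison

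*Protocol article*

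**What the plan says.** All references are to the protocol article.

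- **Label.** Section 4.1 describes a "randomized, placebo-controlled trial with three parallel groups".
- **Arms.** Section 4.7.3 gives controls standard care and the surgeon's routine explanation, with no sham. Section 4.7.2 gives the second VR group a headset session meant to relax and distract.
- **Purpose of the second VR arm.** Section 4.4: "An active comparator VR relaxation/distraction group is included to minimize expectancy and attention-related bias".
- **Primary comparison.** Section 4.9: "The primary comparison will evaluate procedural/educational VR versus standard care with respect to STAI-S score change". It continues: "Secondary comparisons will include relaxation/distraction VR versus standard care and procedural/educational VR versus relaxation/distraction VR".
- **Secondary objectives.** Section 3 lists relaxation VR against standard care, and "procedural/educational VR versus relaxation/distraction VR with respect to postoperative pain, analgesic use, and patient satisfaction". Anxiety is not among these outcomes.
- **Briefing.** Section 4.4: "Participants cannot be fully blinded to VR exposure; however, they will be informed that two different VR experiences are under investigation without emphasis on superiority". Later in the same section: "Participants will be informed that both interventions are active and under evaluation without emphasis on superiority".
- **Endpoint.** Sections 4.7.4 and 4.8 make the primary outcome a questionnaire score, STAI-S, as change from baseline to just after the intervention. The timeline in section 4.5 puts baseline before randomization.
- **Disclosure.** Section 6 lists expectancy effects, incomplete participant blinding, and unequal attention or contact time between the VR groups and standard care.

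**The concern.** The primary endpoint is the patient's own rating, given minutes after the patient learns the allocation. A patient handed a headset has been told that it is an active intervention. A control has been told that two VR experiences are under study and receives neither. Expectation in one group and possible disappointment in the other would both move the primary contrast towards VR.

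The plan names a safeguard, the relaxation arm, but the primary contrast does not use it. The placebo-controlled label then tells readers that non-specific effects have been controlled, which this design does not do for its main result. At stake is how a positive result is read: as an effect of the educational content, or as an effect of the VR session with the expectation and attention that come with it.

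**Working it through.** **1. Is any arm a placebo?**

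| Arm | What it receives | Placebo or sham? |
|---|---|---|
| Educational VR (4.7.1) | standard care plus a 10-minute 360° video | no, it is the test intervention |
| Relaxation VR (4.7.2, 4.4) | standard care plus immersive nature scenes; called an active comparator | no, by the plan's own description |
| Control (4.7.3) | standard care only | no |

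The label in section 4.1 contradicts sections 4.4, 4.7.2 and 4.7.3. This step needs no assumption.

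**2. Can the relaxation arm reduce expectancy bias in the primary contrast?** The contrast is the educational VR mean minus the standard care mean. The relaxation arm's mean does not enter it. In the three-arm ANCOVA that arm contributes to the residual variance and the baseline slope, but it does not remove a shift shared by headset wearers. Only the VR-versus-VR contrast on STAI-S compares two groups that both wear a headset and hear the same message.

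**3. Is that contrast planned for anxiety?** Section 4.9 names it directly after a sentence about STAI-S change, and the ANCOVA on STAI-S has pairwise comparisons, so the natural reading is yes. Section 3 names it for three other outcomes only. The two sections do not match.

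**4. Does baseline adjustment or assessor blinding help?** On the section 4.5 timeline, baseline precedes randomization, so any reaction to allocation lies wholly within the change score and baseline adjustment cannot remove it. Blinded assessors and analysts do not help when the unblinded patient supplies the rating.

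**5. How much could a shift matter? (illustration)** The documents give no expectancy effect, so a shift b of 1 to 4 STAI-S points is assumed, that is 1/8 = 12.5% to 4/8 = 50% of the 8-point target in section 4.3.1.

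Inputs from sections 4.3.1 and 4.9: 42 evaluable per arm, SD 10, two-sided α = 0.05. The enrolment figure reproduces: 42/(1 − 0.15) = 49.4, rounded up to 50. The 42 is taken as stated. The formula 2 × (1.960 + 0.842)² × 10²/8² = 24.5 gives 25 per arm, but that mismatch is a separate matter and does not bear on this point.

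- Standard error = 10 × √(2/42) = 2.18.
- Critical difference = 1.96 × 2.18 = 4.28.
- Chance of rejection with no true effect and shift b = 1 − Φ((4.28 − b)/2.18) + Φ((−4.28 − b)/2.18).

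The plan says pairwise comparisons are Bonferroni-corrected and does not make clear whether the primary one is included, so both levels are shown.

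| Assumed shift b (points) | α = 0.05 | α = 0.05/3 |
|---|---|---|
| 0 | 5% | 1.7% |
| 1 | 7% | 2.9% |
| 2 | 15% | 7% |
| 3 | 28% | 15% |
| 4 | 45% | 29% |

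If baseline adjustment makes the residual SD smaller than 10, the standard error falls and a given shift is declared significant more often.

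**6. What can the VR-versus-VR contrast show?** At 42 per arm and SD 10, power is 96% for an 8-point difference (90% at 0.05/3), but 45% for 4 points (29% at 0.05/3). It can support a large content effect. A non-significant result would not show that content is irrelevant, also because both arms are meant to work.

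**The case against.** A reader might infer four stronger things. The documents do not support them.

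- **That the VR-versus-VR comparison on anxiety is missing.** Section 4.9 lists it as secondary right after naming STAI-S change. What stands is the narrower list in section 3, and that neither section says how the contrast bears on expectancy.
- **That standard care is the wrong primary comparator.** The abstract and section 3 ask whether VR added to standard care beats standard care alone. That is a legitimate package question, and using the relaxation arm in a secondary contrast is coherent. What stands is that section 4.4 credits that arm with protection it cannot give to the primary result.
- **That the risk is concealed.** Section 6 names expectancy, incomplete blinding and unequal attention, and section 4.4 concedes that patients cannot be fully blinded. Disclosure does not correct the label or the briefing.
- **That the briefing itself would produce the rejection rates above.** Patients know whether they wore a headset under any wording, so most open-label expectancy would remain. Nothing in the documents separates the effect of the wording from that of non-blinding. The shift is assumed in size, and its existence and direction are inference. The patient information sheet is not shown, and section 4.4 only summarizes it.

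That controls realize they receive neither VR session is also an inference, though a firm one: there is no sham, and all participants are told that two VR experiences are being studied.

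**Conclusion.** The point holds in a limited form. The placebo-controlled label is wrong on the plan's own description of its arms. The relaxation arm cannot limit expectancy or attention bias in the primary contrast, contrary to what section 4.4 implies. Section 3 and section 4.9 disagree on whether the VR-versus-VR contrast covers anxiety. Telling patients that both interventions are active is neutral between the VR arms but not towards standard care, and may add to an expectancy risk that the plan already concedes.

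The size of that risk cannot be found from the documents. The 7–45% range (3–29% with Bonferroni correction over three comparisons) rests on an assumed shift of 1 to 4 points, SD 10, 42 per arm and no true effect. It shows how sensitive the primary test is to any such shift and does not measure the harm done by the briefing. The primary comparison can stay as it is. The changes below should be made because they are cheap, correct a property the design does not have, and remove an avoidable source of bias.

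**What to change.** 1. In section 4.1, replace the placebo-controlled label with: standard-care-controlled, with an active VR comparator.
2. In section 4.4 and the patient information, use one neutral text for every patient: three ways of preparing for surgery are being compared, and it is not known which is best. Drop the statement that both interventions are active. This reduces expectancy but does not remove it.
3. In section 3, add STAI-S change to the educational-versus-relaxation VR objective, so that it matches section 4.9.
4. In section 4.9, state that a benefit over standard care alone will be reported as the effect of the VR package, including expectation and attention, and not of its educational content.

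The cost is a few reworded sentences, an ethics notification for the patient information, and a slightly more cautious conclusion. No arm, patient or measurement is added.

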### 4.5. Instruments and VR Utilization

The study affects all three groups, and the VR intervention includes only one session. All intervention sessions will be carried out individually. After these assessments, the patients will be oriented to the VR goggles and headset and given tutorials and instructions on how to use the device and how to remove it when they encounter potentially unwanted side effects such as dizziness, headache, nausea, or vomiting. In such cases, the procedure will be stopped and considered a withdrawal.

On the day before surgery, following baseline assessment and informed consent, the researcher will randomly allocate the patients to the VR group, control group, and VR relaxation/distraction group.

The study timeline will proceed as follows: enrollment and informed consent → baseline psychometric and pain assessments → randomization → VR or standard-care intervention on the day before surgery → immediate postintervention assessment → surgery → postoperative assessment within 24 h and analgesic assessment within 24–48 h postoperatively.

VR-related adverse effects, including dizziness, nausea, headache, cybersickness, and visual discomfort, will be prospectively recorded and analyzed descriptively throughout the intervention period.

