#### 4.7.3. Standard Care (Control) Group

In the standard group, patients will only receive standard care and be provided with routine descriptions of the preoperative experience, where a surgeon will explain to them what the preoperative experience will entail.

After VR intervention, psychometric assessments of anxiety, pain score, and satisfaction will be performed and evaluated shortly before the intended surgery. Subsequently, the patients will undergo their planned surgical procedure. Postoperative data on analgesic use and pain will also be collected in the recovery area.

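### A VR session stopped for side effects counts as a withdrawal, without saying whether the patient is still assessed and analysed as randomised

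*Protocol article*

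**What the plan says.** Section 4.5 has patients taught to use the headset and "how to remove it when they encounter potentially unwanted side effects such as dizziness, headache, nausea, or vomiting". The next sentence reads "In such cases, the procedure will be stopped and considered a withdrawal". The article does not say whether this means withdrawal from the session, from the study or from the analysis.

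The same section gives the order of events as "randomization → VR or standard-care intervention on the day before surgery → immediate postintervention assessment". Section 4.7.3 says of the controls: "In the standard group, patients will only receive standard care".

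Section 4.9 states "All analyses will follow an intention-to-treat approach". The primary endpoint, STAI-S change to immediately after the intervention, "will be analyzed using one-way ANCOVA adjusted for baseline STAI-S". On the contrast of interest it says "The primary comparison will evaluate procedural/educational VR versus standard care with respect to STAI-S score change". Multiple imputation with ten imputations is to be used where judged appropriate. The longitudinal analyses rely on mixed models, "which are robust to missing observations under missing-at-random assumptions".

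**The concern.** Stopping a 10-minute session and leaving a trial are different events. A patient who takes the headset off because of nausea is still an inpatient and can usually still complete a questionnaire. If site staff read the sentence as ending participation, the primary outcome is not collected, although it could have been.

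The loss would also be one-sided. Only the VR arms have a session to stop, and the primary contrast sets one of them against standard care. The comparison would drift from all patients offered VR towards those who tolerated it, which is not what an intention-to-treat analysis estimates. A later analysis plan cannot repair this, because a state-anxiety score not taken at that moment cannot be recovered.

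**Working it through.** **1. Can the rule affect both sides of the primary comparison?** No. The trigger is a side effect of the headset (section 4.5), and controls have no session (section 4.7.3). The primary contrast is procedural/educational VR against standard care (section 4.9), so one arm is exposed to the rule and the other is not.

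**2. Does the stop fall before the endpoint?** Yes. Section 4.5 places it after randomisation and before the immediate assessment. Table 2 lists only one STAI-S after baseline, and it is that assessment.

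**3. Is the loss avoidable?** Largely. Table 1 requires admission at least one day before surgery, and section 4.4 sends patients back to their hospital rooms after the session. They remain available for the STAI-S that day and for VAS and analgesic data after surgery.

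**4. Would the planned methods absorb the loss?** Not as described. The ANCOVA adjusts for baseline STAI-S, and the mixed model has group, time and their interaction. Neither contains intolerance, and it is not named as a predictor for imputation. A missing score would in effect be filled in from same-arm patients who tolerated VR. Adding intolerance as a predictor would not help if every stopped patient were unassessed, because no observed scores would exist from which to estimate its effect.

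**5. Size.** Negative change means improvement. Let w be the share of the VR arm stopped, m the mean change in completers, and D the shortfall in improvement of stopped patients relative to completers.

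- All-randomised mean = (1 − w)·m + w·(m + D) = m + w·D
- Overstatement of benefit if stopped patients are dropped = w·D

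The article gives neither w nor D; both are assumptions. The plan does give an attrition figure of 15% for all causes (section 4.3.1), and its inflation step reproduces: 42 / 0.85 = 49.4, rounded up to 50 per arm. I use 15% only as an upper value for w.

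For the false-positive rate I take a true all-randomised effect of zero, SD 10 (section 4.3.1), two-sided α = 0.05, 50 controls against 50(1 − w) VR patients, and a normal approximation:

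- SE = 10·√(1/50 + 1/(50(1 − w)))
- Rate = Φ(−1.96 − wD/SE) + 1 − Φ(1.96 − wD/SE)

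| w | stopped of 50 | D | overstatement (points) | share of 8-point target | false-positive rate |
|---|---|---|---|---|---|
| 2% | 1 | 8 | 0.16 | 2% | 5.1% |
| 5% | 2.5 | 8 | 0.4 | 5% | 5.5% |
| 10% | 5 | 8 | 0.8 | 10% | 6.8% |
| 15% | 7.5 | 8 | 1.2 | 15% | 8.9% |
| 15% | 7.5 | 12 | 1.8 | 22.5% | 13.9% |
| any | – | 0 | 0 | 0% | 5% |

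D = 8 corresponds, for example, to completers improving by 8 points and stopped patients not changing. The all-randomised mean is then 0.95 × (−8) = −7.6 at w = 5% and 0.85 × (−8) = −6.8 at w = 15%.

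**The case against.** The strongest reply is that no removal is stated. The grammatical subject of the sentence is the procedure, and withdrawal from the session is fully compatible with intention-to-treat. The full protocol, which is not shown, may draw the distinction. This stands to the extent that the article contains an unresolved ambiguity and not a proven contradiction. It does not remove the point. Stopping the procedure already ends the session, so calling it a withdrawal as well seems to add a status, and study withdrawal is the more natural reading for staff applying the sentence.

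A reader might go further and infer that the rule strips the worst responders from the VR arms. The article does not support that. The trigger is a physical side effect and not a poor STAI-S change, and there are no data on anxiety in patients who stop. Less benefit in these patients is plausible, but it is not shown.

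A reader might also infer that the main harm of VR is hidden. It is not: adverse effects are recorded prospectively (section 4.5) and are a named secondary outcome (section 4.7.4).

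The stop rate may also be low. Table 1 excludes vertigo, dizziness, motion sickness and claustrophobia, and the video in the primary-comparison arm lasts 10 minutes. Section 4.9 does promise to examine the pattern and mechanism of missing data. So missing-at-random is strained under the study-withdrawal reading, but it cannot be said to fail.

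**Conclusion.** The point holds in a limited form. The article labels as a withdrawal an event that can occur only in the VR arms, after randomisation and before the primary measurement, and leaves its consequence open. Under the study-withdrawal reading it conflicts with the intention-to-treat statement and loses primary data that could have been collected.

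The size is unknown. With an assumed 8-point shortfall, the overstatement runs from 0.16 points at 2% stopped, through 0.4 at 5%, to 1.2 at 15%. With no shortfall it is zero at any stop rate. Much larger figures can be constructed: 15% × 18 points = 2.7 points, or 34% of the target. That requires all the planned attrition in the VR arm to be intolerance of one session, and stopped patients to do 18 points (1.8 SD) worse than completers. The article supports neither.

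The case for acting rests on the one-sidedness of the loss, its irreversibility and the low cost of preventing it, and not on a large demonstrated bias.

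**What to change.** Replace the sentence in section 4.5 with wording such as: *A stopped session is recorded as discontinuation of the intervention and not as withdrawal from the study. Unless the patient withdraws consent, STAI-S, VAS, satisfaction and analgesic use are collected at the times scheduled in Table 2, and the patient is analysed in the assigned arm.* Satisfaction then stays at the post-session assessment, where Table 2 puts it.

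In section 4.9, add a sensitivity analysis for any stopped patient whose post-intervention STAI-S is missing. It should impute a range of unfavourable changes, covering both no improvement and worsening (for example 0, +5 and +10 points), and report how the primary contrast moves.

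The criteria for stopping a session are not touched. The cost is a protocol wording change, one line on the case report form to separate the two events, and one extra analysis; no visit is added. The downside is that the estimated VR effect may be slightly smaller.
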